Over the past decade, a significant body of research has investigated the effects of physical exercise on sleep and the results generally supported the positive impact of physical exercise on sleep (see Kelley et al. [12] for review). Previous studies also support the sleep benefits of physical exercise in children with ASD. For example, we have examined the impact of a basketball training intervention on sleep quality (sleep efficiency and wake after sleep onset) and cognition (inhibition control and working memory) in 40 children with ASD [13]. Research revealed a significant improvement in sleep efficiency and reduction in wake after sleep onset time in the intervention group but not in the control group [13]. Similar sleep benefits following physical exercise were also evident in a more recent study [14], where we showed that jogging intervention had significantly improved sleep efficiency and sleep duration in children with ASD. More remarkably, we also observed that the endogenous melatonin level, as reflected by the 6-sulfatoxymelatonin (aMT6s), was significantly increased within the jogging intervention group, while no change was found in the control group. Physical exercise appears to be capable of modulating the endogenous melatonin level in children with ASD, which in turns improves their sleep quality. If it is so, it is then natural to ask which intervention (i.e. physical exercise or melatonin supplement of the combination of two) is more effective in treating sleep disturbance improving the sleep quality of children with ASD. Without direct comparison, this question remained unanswered. Therefore, here we propose a new study protocol.

This study protocol has two objectives: (1) to determine which intervention is more effective in improving sleep quality in children with ASD and 2) to explain how these interventions impact on sleep via melatonin-mediated mechanism model. We hypothesise that the combination intervention (i.e. jogging and melatonin supplement) is the most effective because it may provide sufficient melatonin level to enhance sleep quality through both physical exercise and melatonin supplement.

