### Participants

Participants will be screened using the following inclusion criteria: (1) clinical diagnosis of ASD by a physician based on the Diagnostic and Statistical Manual of Mental Disorders, 5th edition, (DSM-5) [15]; (2) age 8–11 years; (3) pre-puberty as indicated by Tanner stage I through screening by a physician (to prevent any puberty influence on hormonal response); (4) being given an average of 8 hours of sleep per night by their parents over the past 3 months; (5) parents reported sleep onset delays of 30 minutes of longer on three or more nights per week; (6) free of psychotropic medications (allergy medications and medications for constipation are allowed); (7) non-verbal IQ over 50 using a brief version of Wechsler intelligence scale for children (Chinese revised, C-WISC) [16] (since lower IQ is liked to higher prevalence of comorbid psychiatric disorders and seizures); (8) Social Response Scale T-score 80 or above (to control for the ASD severity) and (9) no concurrent medication for at least three months before the study or any prior melatonin treatment.

Exclusion criteria are: (1) with one or co-morbid psychiatric disorders; (2) with other medical conditions that limit their physical exercise participation and sleep (e.g., asthma, seizure, cardiac disease etc); and (3) with a complex neurologic disorder (e.g., epilepsy, phenylketonuria, fragile X syndrome, tuberous sclerosis) and (4) participants who are currently meeting physical exercise guidelines (i.e. 60 minutes of moderate and vigorous physical exercise each day).

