### Randomization

Participants will be randomly assigned to three intervention groups or a placebo-control group by a trained research staff using MS Excel randomization function. Block randomization with block size of 5 will be used for equal allocation ratios.

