### Statistical methods

All statistical analyses will be conducted using SPSS (version 26.0) for Windows (SPSS Inc., Chicago, IL, USA). All the data will be entered into SPSS by the research assistant. One-way (4 Groups: physical exercise vs melatonin supplement vs combined exercise and melatonin supplement vs placebo-control) analysis of variances (ANOVA) with repeated measures will be performed to compare changes in actigraphy data and endogenous melatonin level between and within groups over different time points (i.e. T1-T3). Post-hoc analyses will be performed when any significant difference both between- and within-group is found in any of the outcome variables. Bonferroni correction will be used to adjust the alpha levels. Depending on the proportion of missing data and the assumption of normality, multilevel regression or a generalized estimating equation (GEE) will also be used as a sensitive analysis to assess the effects of the physical exercise intervention, melatonin supplement, time effect, and their interaction with sleep outcomes and melatonin level outcomes if there is any missing data. Average time spent in both daily sedentary activity and MVPA at baseline will be used as covariates. Linear regression will be used to analyse the association between participant’s adherence to the intervention and the outcome variables as a secondary analysis. Mediation analysis will be conducted to examine the mediating effect of endogenous melatonin level at T2 on the relation between physical exercise and sleep at T3. Preacher and Hayes’ bootstrapping and conditional process modeling will be used to determine the significance of the mediating effect. A p-value of <0.05 will be considered statistically significant. Both proposal analysis and intention-to-treat analysis will be carried out. Demographic variables (e.g. age, sex, BMI) will be adjusted if they demonstrate clinically significant prognostic effects on the outcomes (with absolute correlation or Cohen’s d effect size of >0.2) for both main analysis and mediation analysis.

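### Change is tested within arms as well as between arms, the post-hoc trigger is ambiguous, and the plan does not say that the between-arm contrast decides effectiveness

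*Protocol article*

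**What the plan says.** The objective in the Introduction is comparative: "to determine which intervention is more effective in improving sleep quality in children with ASD". Under Randomization, "Participants will be randomly assigned to three intervention groups or a placebo-control group", so a concurrent randomised control exists.

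Statistical methods names one model, a four-group ANOVA with repeated measures at T1, T2 and T3, used to "compare changes in actigraphy data and endogenous melatonin level between and within groups over different time points (i.e. T1-T3". It continues: "Post-hoc analyses will be performed when any significant difference both between- and within-group is found in any of the outcome variables". Then: "Bonferroni correction will be used to adjust the alpha levels" and "A p-value of <0.05 will be considered statistically significant". A multilevel or GEE sensitivity analysis would examine exercise, melatonin, time and their interaction.

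Two further places bear on the point. Participants admits a child if "parents reported sleep onset delays of 30 minutes of longer on three or more nights per week". The Introduction reports the melatonin marker in the earlier jogging study as a result that "was significantly increased within the jogging intervention group, while no change was found in the control group".

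**The concern.** Only a comparison of change between arms can answer which intervention is better. A T1-T3 test inside one arm mixes the treatment effect with everything else that moves sleep over ten weeks, and the other arms share that movement. Finding significance in one arm and not in another is not a test of the difference between them.

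Statistical methods puts the two kinds of comparison on the same footing. The trigger sentence does not separate them, because its wording has two readings:

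- **Strict reading:** a between-group and a within-group difference must both be present before post-hoc tests are run.
- **Loose reading:** a significant difference of either kind is enough. A time effect common to all four arms would then open within-arm testing.

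Under the loose reading, a result such as combination improved and control did not could be reported although the arms do not differ. With three active arms to rank, there are several chances for such a pattern.

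**Working it through.** **The plan's own figure.** Sample size calculation gives 20 per group for d of about 0.9, 80% power and a 5% level. The normal approximation for two arms gives 2 × (1.960 + 0.842)² / 0.9² = 2 × 7.85 / 0.81 = 19.4, so 20. The exact t calculation gives 21, with 79.2% power at 20. The stated figure is therefore reproduced, and it fits a comparison of two arms.

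**Inputs**
- From the document: four equal arms, 25 recruited per arm, 25% attrition. This leaves 25 × 0.75 = 18.75, taken as 19 per arm.
- From the document: 5% level (two-sided assumed).
- Assumed, because the document gives neither: a shared improvement of 0 to 0.4 SD in every arm, and a T1-T3 correlation ρ of 0.5 to 0.7.
- Assumed: a Bonferroni family of three time pairs.

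**Step 1: one arm on its own.** The SD of change is √(2(1 − ρ)), which is 1.00 at ρ = 0.5 and 0.775 at ρ = 0.7. With a shared shift of 0.4 SD, the paired test in one arm is significant with probability p = 0.378 (ρ = 0.5) or 0.566 (ρ = 0.7). With Bonferroni over three, p = 0.211 or 0.371.

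**Step 2: at least one active arm significant, control not.** The arms are independent and share the same p, so the probability is (1 − p) × [1 − (1 − p)³].

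| Shared shift | ρ | Adjustment | p | Result |
|---|---|---|---|---|
| 0 | any | none | 0.05 | 0.95 × (1 − 0.857) = 14% |
| 0 | any | Bonferroni/3 | 0.0167 | 0.983 × (1 − 0.951) = 5% |
| 0.4 SD | 0.5 | none | 0.378 | 0.622 × (1 − 0.241) = 47% |
| 0.4 SD | 0.7 | none | 0.566 | 0.434 × (1 − 0.082) = 40% |
| 0.4 SD | 0.5 | Bonferroni/3 | 0.211 | 0.789 × (1 − 0.491) = 40% |
| 0.4 SD | 0.7 | Bonferroni/3 | 0.371 | 0.629 × (1 − 0.249) = 47% |

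The expression peaks where (1 − p)³ = 1/4, at 0.630 × 0.75 = 47%. Simulated values scatter around this, up to 48%. At a shift of 0.2 SD, simulation gives 30% to 37% unadjusted and 15% to 22% with Bonferroni. Some but not all of the four arms are significant in 83% to 86% of trials at 0.4 SD, unadjusted. Bonferroni gives no dependable protection, because it lowers the chance of significance in the control arm too.

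**Step 3: the between-arm test.** In 10,000 simulated trials per setting with 20 per arm and three visits, the group-by-time F test rejects in 4.6% to 5.4% of trials whatever the shared shift.

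**Step 4: the two readings of the trigger.**
- Strict: with the group-by-time test also required, the misleading pattern occurs in 1.6% to 3.0% of trials for shifts of 0.2 to 0.5 SD.
- Loose: the overall time effect alone is significant in 43% (ρ = 0.5) or 65% (ρ = 0.7) of trials at a shift of 0.2 SD, and in 80% or 95% at 0.3 SD. The within-arm tests would then usually be opened. With no shared shift, the time effect is significant in only about 5%, so the 14% in the table applies to within-arm tests run without any prior condition.

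**The case against.** The strongest reply is that the plan contains no rule that counts within-arm significance as efficacy. Comparing between and within groups is ordinary wording for a design with group as the between-subject factor and time as the within-subject factor. The same sentence compares change against a randomised placebo arm, which removes change shared by all arms. The sensitivity analysis includes interaction terms, and the sample size fits a two-arm comparison. Read strictly, the trigger already holds the error to about 2% to 3%. The deciding contrast may also be named in an analysis plan that is not shown.

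Most of this stands, and it rules out three stronger readings that a reader might infer:

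- **That shared change will be credited to whichever arm reaches significance.** No text says so. It is a risk under one reading of the plan.
- **That regression to the mean will drive improvement in every outcome.** Children are selected on parent-reported sleep onset delay, not on actigraphy or urinary melatonin, so the effect is weaker for the outcomes named in the ANOVA sentence. It applies most directly to the parent questionnaire and sleep log. The calculation does not depend on this mechanism, since any shared change has the same effect.
- **That the Introduction's account of earlier studies shows how this trial will be judged.** It is a short summary, and whether those studies also tested group-by-time cannot be seen here. It shows only that the contrast of a changed arm with an unchanged one is a familiar way to describe such results.

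What the reply does not remove is the wording itself. Within-group comparison is stated, the trigger has two readings, and a between-arm test that is present but not decisive does not prevent the pattern. At a 0.4 SD shared shift, the pattern still appears in 39% to 47% of trials in which the between-arm F test is not significant (unadjusted). This concerns what the article states, not detail left for later.

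**Conclusion.** The point holds as an ambiguity to be corrected, not as an error that the plan is bound to make. Statistical methods tests change both ways, has a trigger that can be read loosely, and does not tie the comparative objective to the between-arm contrast. If arms were judged on their own T1-T3 tests, a difference between an active arm and control could be claimed falsely in about 14% to 47% of trials unadjusted (5% to 47% with Bonferroni over three), against about 5% for the between-arm test. These figures rest on the assumed shift, correlation and Bonferroni family, and on no true difference between arms. They describe a possible use of the within-arm tests, not a stated decision rule. The change should be made, because the correction is nearly free and the within-arm tests cannot answer the trial's question.

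**What to change.** State in Statistical methods that:

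1. Every statement on effectiveness or ranking rests only on the between-arm contrast, either group-by-time or T3 compared between arms with adjustment for T1, reported with confidence intervals.
2. Post-hoc pairwise comparisons between arms follow only a significant between-arm result, with the Bonferroni correction applied to those comparisons. A significant time effect alone opens no post-hoc test.
3. Within-arm change is shown as description, without p-values, and is not used to judge or rank the interventions.

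Adjusting T3 for T1 uses data already collected. Relative to a change score, the variance ratio is (1 − ρ²) / (2(1 − ρ)) = (1 + ρ)/2, which is 0.75 at ρ = 0.5 and 0.85 at ρ = 0.7. That is a 15% to 25% reduction under the assumed correlations.

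The cost is a few sentences, with no change to design, sample size or data collection. The downside is that within-arm p-values can no longer be reported as evidence.

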### Sample size calculation

Previous study [13, 14] showed physical exercise had notable effects (corresponding to a Cohen’s *d* of about 0.9) on improving sleep onset latency, sleep duration and sleep duration. We assumed that melatonin supplements have similar effects on sleep. A sample of 20 participants per group is computed by G*power software to achieve a power of 80% and a level of significance of 5% and 95% confidence level. Assuming 25% attrition rate, 25 participants per group will be recruited (i.e. the total number is 100).

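### The post-hoc comparisons are adjusted by plain Bonferroni, which is valid but, for testing, dominated by Holm's step-down procedure at the same 5% family-wise error

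*Protocol article*

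**What the plan says.** The Statistical methods section of the protocol article plans a "One-way (4 Groups: physical exercise vs melatonin supplement vs combined exercise and melatonin supplement vs placebo-control) analysis of variances (ANOVA) with repeated measures" over T1 to T3 for the actigraphy and melatonin outcomes. It then states: "Post-hoc analyses will be performed when any significant difference both between- and within-group is found in any of the outcome variables". The next sentence is the whole of the multiplicity rule: "Bonferroni correction will be used to adjust the alpha levels". The nominal level is given as "A p-value of <0.05 will be considered statistically significant". No step-down or closed procedure is named, and the article does not say which tests make up the Bonferroni family.

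The Introduction sets the aim of finding out which intervention works better and adds: "We hypothesise that the combination intervention (i.e. jogging and melatonin supplement) is the most effective". The Sample size calculation section rests on earlier work in which "physical exercise had notable effects (corresponding to a Cohen’s" d of about 0.9), and continues: "We assumed that melatonin supplements have similar effects on sleep". It concludes: "A sample of 20 participants per group is computed by G*power software to achieve a power of 80% and a level of significance of 5" per cent.

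**The concern.** The ANOVA can show that the four groups are not all alike. It cannot show which intervention is better, or that the combination is best. Those answers come from comparisons between pairs of groups, which are the comparisons the correction applies to.

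Plain Bonferroni holds every comparison to the same strict threshold, however many others have already been rejected. Holm relaxes the threshold after each rejection, keeps the same strong family-wise control and needs no added assumption. Since it never rejects less, a plan whose purpose is to order four arms gives up some power by choosing the single-step version. The sample size was set at an unadjusted 5% level, so no children were added to absorb the cost of a correction.

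**Working it through.** **Inputs.** From the article: four equal groups, d of about 0.9 for exercise and a similar value for melatonin, 5% level, 80% power, 20 per group before attrition. Assumed here: two-sided tests; a family of the six group pairs (4 × 3 / 2 = 6) within one outcome; one normally distributed change score per child with unit SD; and the patterns of means below. The article gives no effect size for the combination.

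**The plan's own figure.** By the normal approximation, n = 2(z₀.₉₇₅ + z₀.₈₀)² / d² = 2(1.960 + 0.842)² / 0.81 = 19.4, so 20 per group. The exact t-test gives 21, with 79.2% power at 20. The stated 20 is therefore reproduced for a single pair at an unadjusted 5%. At 0.05/6 = 0.00833, power for one pair at n = 20 is 53% with a two-sample t-test, or about 55% with the variance pooled over four groups (4 × 20 − 4 = 76 df).

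**The rules compared.** Sort the six p-values from smallest to largest, compare each with 0.05 divided by its divisor, and (for the step-down rules) stop at the first failure.

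- Bonferroni: divisor 6 throughout, so every threshold is 0.00833.
- Holm: divisors 6, 5, 4, 3, 2, 1, so thresholds 0.00833, 0.0100, 0.0125, 0.0167, 0.025, 0.05.
- Shaffer: divisors 6, 3, 3, 3, 2, 1. If at least one of the six equalities among four means is false, at most three can be true (three means equal and one different). This holds only for exactly this family.

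Every Holm threshold is at least as large as Bonferroni's, so Holm rejects whatever Bonferroni rejects.

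**Simulation.** 100,000 trials per pattern, 20 per arm, an omnibus F-test at 5% as the gate, then six pooled-variance t-tests. Means are in the order control, exercise, melatonin, combination.

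| Means | True difference | Bonferroni | Holm | Shaffer |
|---|---|---|---|---|
| 0, 0.9, 0.9, 0.9 | each active arm vs control | 55.5% | 58.5% | 62.4% |
| | at least one found | 78.8% | 78.8% | 78.8% |
| | all three found | 31.0% | 37.0% | 41.8% |
| 0, 0.9, 0.9, 1.35 | each single arm vs control | 55.8% | 61.1% | 65.5% |
| | combination vs each single arm | 10.5% | 14.4% | 16.2% |
| | combination vs control | 93.6% | 94.0% | 94.5% |
| | all five found | 0.9% | 3.6% | 3.6% |
| 0, 0.9, 0.9, 1.8 | each single arm vs control | 55.8% | 65.5% | 67.3% |
| | combination vs each single arm | 55.5% | 65.4% | 67.1% |
| | combination vs control | 99.8% | 99.8% | 99.8% |
| | all five found | 13.6% | 29.8% | 30.0% |

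Leaving aside combination versus control, where power is already at least 93%, Holm's gain runs from 58.5 − 55.5 = 3.0 to 65.4 − 55.5 = 9.9 points. Shaffer's runs from 16.2 − 10.5 = 5.7 to 67.1 − 55.5 = 11.6 points.

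**Family-wise error for one outcome.** With all means equal and the gate in place, it was 3.8% for all three rules. With only some means equal, Bonferroni reached at most 2.3%. The step-down rules reached at most 5.06%, which is the nominal 5% within the simulation standard error of 0.07 points.

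**The case against.** The strongest reply is that nothing here is an error. Bonferroni is standard and valid, and it gives tests and simultaneous intervals that agree with each other. That stands: this is a loss of efficiency, not a fault in error control.

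Second, the family is inferred. The sentence before the correction covers between-group and within-group differences in any outcome, so the family might include pairs of time points, or several outcomes. That also stands. Holm would still never reject less than Bonferroni in another family, but the figures above would not apply, nor would Shaffer's divisors.

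Third, the larger gains need a fully additive combination at d = 1.8, which the article does not state. A reader might take the rise from 13.6% to 29.8% for all five differences as the expected benefit, but the documents do not support that. At 1.35, the comparison of the combination with a single arm stays weak under any rule, at 10.5% to 16.2%.

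A reader might also infer that the plan pays twice for the same error, because a significance gate comes before a division by six, and that the first divisor could be 3. That requires the gate to be the omnibus group test on the same outcome. The wording mixes between-group and within-group effects and does not clearly define such a gate. Without the omnibus gate, starting at divisor 3 gives a family-wise error of 7.7% when all means are equal.

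Finally, it is tempting to say that Bonferroni buys nothing. It buys matching intervals. These matter because the Discussion section contemplates concluding that the three interventions are equally effective, a conclusion that needs interval estimates rather than more rejections.

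**Conclusion.** The point holds as a recommendation on efficiency. For testing, Holm dominates the stated correction at the same 5% family-wise error, and this does not depend on the effect sizes. The size of the gain does. With six pairs within an outcome and 20 per arm, it is about 3 to 10 points per true difference with Holm and about 6 to 12 with Shaffer, over the patterns assumed and apart from comparisons already near certain.

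Two limits apply. Holm and ordinary Shaffer both start at 0.05/6, so the chance of finding at least one difference does not change; the benefit is in the second and later comparisons, which ranking the arms requires. And the change does not make up for a sample size set at an unadjusted 5%, which is a separate matter. The 5% here is for each outcome; neither procedure, applied within an outcome, controls error across the several sleep and melatonin outcomes.

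**What to change.** Replace the Bonferroni sentence in the Statistical methods section with:

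> Pairwise comparisons among the four groups will be adjusted by Holm's step-down procedure within each outcome, with family-wise alpha 0.05.

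This also settles the family. Shaffer's divisors may be named instead, but only if the family is exactly the six pairs of the four groups.

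The cost is one sentence, plus sorting six unadjusted p-values per outcome. The drawback should be stated in the plan: step-down tests have no directly matching simultaneous intervals. If Bonferroni intervals are reported alongside, one may include zero for a pair that Holm declares significant, for example when the second-smallest p-value lies between 0.00833 and 0.0100 and the smallest is below 0.00833.

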### Study measures

The demography and developmental history of each participant will be obtained from their parents or schools. And the following measurements will be carried out at T1, T2 and T3.

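### The main repeated-measures ANOVA would normally leave out every child with a missing visit, while the model that uses all visits is only a sensitivity analysis and no analysis is named as deciding

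*Protocol article*

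**What the plan says.** All of this is in the protocol article. Under Statistical methods, a four-group "analysis of variances (ANOVA) with repeated measures will be performed to compare changes in actigraphy data and endogenous melatonin level between and within groups", over T1 to T3. The software is fixed: "All statistical analyses will be conducted using SPSS (version 26.0) for Windows". Study measures sets three assessments: "the following measurements will be carried out at T1, T2 and T3".

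The methods that can use incomplete children come second: "multilevel regression or a generalized estimating equation (GEE) will also be used as a sensitive analysis". Their use is introduced by "Depending on the proportion of missing data and the assumption of normality", with no threshold, and the same sentence closes with "if there is any missing data".

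On analysis sets, the section says: "Both proposal analysis and intention-to-treat analysis will be carried out". 'Proposal' is not explained; per-protocol appears to be meant. Neither set is called primary.

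Under Sample size calculation, loss is expected: "Assuming 25% attrition rate, 25 participants per group will be recruited".

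**The concern.** The plan ranks its methods, and the one placed first cannot include a child who lacks T1, T2 or T3 unless values are imputed. The article does not say that children are dropped. That follows from how the named procedure works and from the absence of any imputation step. With 25% attrition built into the sample size, the main result would be a comparison of completers. A dropout who wore the actigraph and gave urine at T1 and T2 would contribute nothing to it.

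Two arms (jogging and combination) require 50 sessions before school and two do not. Dropout could therefore differ between arms and could depend on how a child was sleeping by T2. If so, completers are no longer comparable by randomisation.

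The trial is meant to say which intervention is most effective. If the ANOVA, the multilevel or GEE analysis, the intention-to-treat analysis and the 'proposal' analysis disagree, no rule says which answer counts.

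**Working it through.** **Inputs from the protocol.** d = 0.9, 80% power, 5% significance, 20 per group before attrition, 25% attrition, 25 per group, 100 in total (Sample size calculation); three visits (Study measures). Two-sided testing is assumed, as sidedness is not stated.

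**1. The plan's own figures.**
- Normal approximation: n = 2 × (1.96 + 0.84)² / 0.9² = 19.4, rounded up to 20 per group. This reproduces the stated 20. The exact t-test calculation gives 21.
- Attrition: 20 × 1.25 = 25 reproduces the stated 25. Dividing instead, 20 / 0.75 = 26.7, gives 27 per group.

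**2. Children in the main test as planned.**
- Per arm: 25 × 0.75 = 18.75. In total: 100 × 0.75 = 75. About 25 randomised children are absent.

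**3. Pairwise power at d = 0.9** (two-sided 5% t-test, before any Bonferroni correction):

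| n per arm | Power |
|---|---|
| 18 | 74.6% |
| 19 | 77.0% |
| 20 | 79.2% |
| 21 | 81.2% |
| 25 (nothing missing) | 87.7% |

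**4. What the all-visits model recovers.** If dropouts leave after T2, a likelihood model has information on the T3 mean equivalent to 18.75 / (1 − 0.25 r²) children per arm, where r is the T2–T3 correlation (assumed; not in the protocol).
- r = 0.5: 18.75 / 0.9375 = 20.0.
- r = 0.7: 18.75 / 0.8775 = 21.4.

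This is the best case, because it takes every dropout to have a valid T2.

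**5. Bias, by illustrative simulation** (true T1 to T3 difference 0.9 SD, dropout after T2; correlations and dropout mechanisms assumed):

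| Correlations | Dropout, arm 1 / arm 2 | Completers | Likelihood |
|---|---|---|---|
| all 0.6 | three patterns, same or different by arm | 0.900–0.901 | 0.900–0.902 |
| T1–T2 0.5, T2–T3 0.7, T1–T3 0.4 | 25% / 25%, same T2 dependence | 0.900 | 0.901 |
| same | 25% / 25%, T2-dependent in arm 1 only | 0.956 | 0.900 |
| same | 35% / 15%, T2-dependent in arm 1 only | 0.979 | 0.905 |

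Bias in the T1 to T3 change needs both a different dropout mechanism by arm and unequal correlations. Even then it is 0.06 to 0.08 SD here. With no true effect and T2-dependent dropout in one arm only, completers' T1 to T3 change differed by 0 to 0.08 SD. Their T1 to T2 change, which also feeds the group-by-time test, differed by 0.06 to 0.14 SD.

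**The case against.** **The all-data result would be seen anyway.** The sentence on the alternative models ends with "if there is any missing data", a condition that 25% attrition would meet. The opening clause can also be read as choosing between multilevel regression and GEE. This largely stands: the model would very probably be run. It would still be run as a sensitivity analysis, with no rule for when it overrides the ANOVA.

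**The plan promises intention-to-treat, and detail may sit elsewhere.** A reader might infer that the plan contradicts its own intention-to-treat commitment. The text does not go that far. It names no leading analysis set, and an ANOVA on imputed data would be compatible with it. Imputation rules and set definitions are commonly left to the full protocol or SAP, so their absence is no fault. What remains is the ranking of methods, which the article does fix.

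**Inflated false positives.** A reader might infer a false-positive rate of 7 to 9%. In simulation that belongs to a bare comparison of T3 means under strong T2-related dropout in one arm and random dropout in the other. The plan compares changes. In the same scenario the T1 to T3 change comparison rejected in 4.8 to 5.6% of trials and a multivariate group-by-time test in 5.6 to 7.1%. No protocol figure supports the scenario itself.

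**Power as low as 69%.** This needs a further 5% of children to have a void recording at each visit: 25 × 0.75 × 0.95³ = 16.1 per arm. The 5% is an assumption. The Sleep paragraph voids individual nights within a seven-day recording, not children, and the rule does not touch urinary melatonin.

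**The power gap is an inflation matter.** The shortfall from 20 to 18.75 arises because 20 was multiplied by 1.25 and not divided by 0.75. That is true and is a separate point. It does not alter the exclusion of about 25 randomised children.

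**Conclusion.** The point holds in limited form. As the method is normally run in SPSS, and with no imputation named, the main test uses about 75 of 100 randomised children, or 18 to 19 per arm. Unadjusted pairwise power is then about 75 to 77% at d = 0.9, and dropouts' T1 and T2 data are discarded. These figures rest only on the plan's own attrition and effect size and on two-sided t-tests.

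Bias is possible but not shown. It depends on arm-specific, T2-related dropout and on the correlation pattern, and it is near zero to small for T1 to T3 change. Figures of 7 to 9% false positives or 69% power should not be cited except as labelled illustrations.

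The lack of a deciding analysis rests on no assumption. This should be fixed before the data are analysed, but it is not a defect that undermines the trial.

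**What to change.** In Statistical methods, name one deciding analysis: a likelihood-based multilevel (mixed) model with arm, visit and arm-by-visit, in all randomised children as allocated, using every available visit. Call it the primary intention-to-treat analysis. Adjusting for the T1 value is an optional refinement.

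Keep the completers ANOVA and the 'proposal' analysis (defining that term) as sensitivity analyses, run whatever the amount of missing data.

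Do not treat unweighted GEE as interchangeable with the likelihood model. It generally needs data to be missing completely at random, whereas the likelihood model needs only missing at random.

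The cost is wording. The plan already names the multilevel model and SPSS 26 fits it; no further data, participants or software are needed.
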